### Baseline Characteristics

Comorbidities are determined using all available data in the linked healthcare databases (from 2002 until date of randomization), and require either one hospital diagnosis or two community diagnoses. Chronic kidney disease (CKD) is additionally defined by laboratory data when eGFR < 40 mL/min/1.73m^2 on 2 occasions > 3 months apart.

### Selecting regression covariates

Analyses of dichotomous outcomes will use a maximum of 1 covariate per 10 outcomes, and analyses of continuous outcomes will use a maximum of 1 covariate per 20 randomized subjects. The covariate list for each analysis is predefined in table 2, and all are measured at baseline. We will always use the maximum number of covariates possible, selected in the order given (i.e. we will not undertake stepwise addition or subtraction). As we go down the covariate list, if one covariate has too many levels to be accommodated by the remaining number of outcomes or participants (e.g. facility, or level of care) we will skip it and go to the next covariate in the list.

| Table 2 Analysis Plan        |                          |                                                                                                  |
|-------------------------------------|--------------------------|--------------------------------------------------------------------------------------------------|
| Outcome                      | Method            | Baseline Covariates                                                                       |
| Primary                      |                          |                                                                                                  |
| Major adverse cardiovascular events | Cox Proportional Hazards | Age <70, Gender, Facility/Level of Care specific mortality rate (prior 3 years), New admission*, |

|                                                                                     |                          |                                                                                                                                                                                                                                                                                                                                |
|-------------------------------------------------------------------------------------|--------------------------|--------------------------------------------------------------------------------------------------------------------------------------------------------------------------------------------------------------------------------------------------------------------------------------------------------------------------------|
|                                                                                     |                          | Old admission † , Days hospitalized in prior 6 months, Number of ED visits in prior 6 months, Charlson score, Facility, Total number of non-BP medications, Total number of BP medications, CHF, COPD, CKD, stroke, diabetes, CAD, sleep apnea                                                                      |
| Secondary Efficacy                                                           |                          |                                                                                                                                                                                                                                                                                                                                |
| All-cause mortality                                                                 | Cox Proportional Hazards | Same as for primary outcome                                                                                                                                                                                                                                                                                                    |
| Hospitalization for stroke
Hospitalization for MI/ACS
Hospitalization for CHF | Cox Proportional Hazards | Facility/Level of Care specific hospitalization rate (prior 3 years)                                                                                                                                                                                                                                                           |
| All-cause unplanned hospitalization / ED visit                                      | Cox Proportional Hazards | Facility/Level of Care specific hospitalization rate (prior 3 years), New admission*, Old admission) † , Days hospitalized in prior 6 months, Number of ED visits in prior 6 months, Charlson score, Age < 70, Gender, Total number of non-BP medications, Total number of BP medications, CHF, COPD, CKD, Diabetes |
| Secondary Safety (non-cognitive)                                             |                          |                                                                                                                                                                                                                                                                                                                                |
| Non-vertebral fracture                                                              | Cox Proportional Hazards | Facility/Level of Care specific non-vertebral fracture rate (prior 3 years), prior non-vertebral fracture, Gender, Age < 70, New admission*, Old admission †                                                                                                                                                        |
| Fall in the last 30 days                                                            | Poisson Regression       | Facility/Level of Care specific prior % fallers ‡ , Facility/Level of Care specific non-vertebral fracture rate (prior 3 years), New admission*, Old admission † , Gender                                                                                                                                |
| Urinary incontinence                                                                | Poisson Regression       | Facility/Level of Care specific prior % incontinent ‡ , New admission*, Old admission † , Age < 70, stroke, gender, diabetes                                                                                                                                                                             |
| Full thickness skin ulceration (stage 3 or 4)                                       | Poisson Regression       | Facility/Level of Care specific prior % ulcerated, ‡ New admission*, Old admission † , Stroke, Number of BP medications, Age < 70, gender                                                                                                                                                                |
| Secondary Safety (cognitive-behavioral)                                      |                          |                                                                                                                                                                                                                                                                                                                                |

|                                                                                                                                                                                                                                                                                                                                                                                              |                            |                                                                                                                                                                                                                                                                                                            |
|----------------------------------------------------------------------------------------------------------------------------------------------------------------------------------------------------------------------------------------------------------------------------------------------------------------------------------------------------------------------------------------------|----------------------------|------------------------------------------------------------------------------------------------------------------------------------------------------------------------------------------------------------------------------------------------------------------------------------------------------------|
| “Deteriorated cognition relative to status 90 days prior”                                                                                                                                                                                                                                                                                                                                    | Poisson Regression         | Facility/Level of Care specific prior % deteriorated ‡ , Age <70, New admission*, Old admission † , gender                                                                                                                                                                           |
| “Behavioral symptoms that are present a minimum of 4 days per week and not easily altered” (Includes wandering, verbal abuse, physical abuse, socially inappropriate or disruptive behavior, and resisting care)                                                                                                                                                                             | Poisson Regression         | Facility/Level of Care specific prior % behavior problems ‡ , New admission*, Old admission † , Gender, Age < 70, Days hospitalized in prior 6 months, Number of ED visits in prior 6 months, Total number of non-BP medications, Total number of BP medications, Charlson score     |
| Receipt of antipsychotic medication or physical restraints in the last 7 days                                                                                                                                                                                                                                                                                                                | Poisson Regression         | Same as above                                                                                                                                                                                                                                                                                              |
| Receipt of anti-anxiety medication on ≥3 of the last 7 days                                                                                                                                                                                                                                                                                                                                  | Poisson Regression         | Same as above                                                                                                                                                                                                                                                                                              |
| Receipt of a bedtime sleeping pill on ≥3 of the last 7 days                                                                                                                                                                                                                                                                                                                                  | Poisson Regression         | Same as above                                                                                                                                                                                                                                                                                              |
| “Indicators of depression or anxiety almost daily” in the last 30 days                                                                                                                                                                                                                                                                                                                       | Poisson Regression         | Same as above                                                                                                                                                                                                                                                                                              |
| Cost                                                                                                                                                                                                                                                                                                                                                                                  |                            |                                                                                                                                                                                                                                                                                                            |
| Acute care costs

Total cost of care                                                                                                                                                                                                                                                                                                                                                   | Multiple Linear Regression | Facility, Level of Care § , Age <70, New admission*, Old admission † , Gender, Days hospitalized in prior 6 months, Number of ED visits in prior 6 months, Charlson score, Total number of non-BP medications, Total number of BP medications, CHF, COPD, diabetes, CAD, stroke, CKD |
| * Resident in current facility less than 60-days at time of randomization
† Resident in current facility more than 3-years at time of randomization
‡ % of all RAI-MDS reports from this facility over the last 3-years indicating this outcome
§ In order of increasing care, this includes: Levels 3, 4, 4D, and 5 (as described in the manuscript under Setting and Recruitment) |                            |                                                                                                                                                                                                                                                                                                            |

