#### **D) Power/Sample Size Estimate:**

Expected Recruitment: At the time of this application we are collaborating with multiple ICCER-affiliated LTC organizations that wish to participate in this initiative. Most of these organizations have multiple facilities, many of which have multiple buildings or wings. Using Canadian Primary Care Sentinel Surveillance (CPCSSN) EMR data (accessed for the purpose of this application) we know that 53% of Canadians 80 yrs and older are listed as currently taking daily BP lowering medication. In our experience most of these medications are maintained upon nursing home admission. This suggests, given the 18-month median lifespan of newly admitted patients (and 9 month median lifespan of those already resident at the time of the study), that we should easily obtain 1200 residents total over the roughly 2-3-year duration of the trial.

Power: Utilizing well described methods for sample size determination, inflating the number of events to account for noncompliance, conservatively setting the median lifespan at 3 years to account for the inclusion of supportive living residents who, on average, live longer than the expected 18 months in long-term care facilities and assuming 33% of patients will be censored prior to any events, we find that 1232 patients would have 80% power (at a p of 0.05) to detect a difference between groups in the primary outcome of 27.6%. Although smaller differences would still be clinically meaningful, this difference is less than the 55% relative reduction in total mortality claimed in the MAPEC trial that we are trying to reproduce, and it is a very conservative minimum estimate for the actual power that the study will have. Additional power, while not directly calculable, will come in 2 ways: 1) These calculations assume no meaningful covariates and we have several covariates that are likely to be predictive of each outcome – in particular the resident's

level of care designation, and 2) we will continue to seek new facilities to partner with over the course of the trial – which should increase the number of residents available.

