## PLAN FOR DATA ANALYSIS:

**Interim Analysis:** An independent data safety monitoring board (DSMB) organized and chaired by [name] (Cochrane Hypertension Review Group Coordinating Editor) will review all data upon reaching 150 events (~18 months in). If  $p \leq 0.001$  for benefit (the

Haybittle-Peto boundary – recommended to reduce the chance of stopping too early and magnifying benefit), or if  $p \leq 0.05$  for harm, the DSMB will apply clinical judgement and make recommendations to the steering committee on whether the trial should break early.

**Statistical Analysis:** The primary outcome will be analyzed by a Proportional Hazards Survival Analysis using multiple patient level covariates including: Age <70, Gender, Location (Edmonton / Calgary / Other), New admission (< 60 days on date of randomization), Old admission ( $\geq 3$  years on date of randomization), Level of Care Designation (i.e. LTC, LTC-D, SL-D, SL, PSL), Days hospitalized in the prior 6 months, Number of ER visits in the prior 6 months, Charlson score, Total number of medications, Total number of BP medications, Dementia. Our AHS data team will be connecting with facilities approximately once per month to determine level of care designation (i.e LTC, LTC-D, SL, SL-D) on each new resident who is eligible to participate in BEDMED-Frail. The purpose of this data is to allow for adjustment of this variable, listed above.

**THE CASE FOR RANDOMIZATION WITH A WAIVER OF CONSENT:** As important as this work is, it is not feasible without a waiver of consent and it is important to clearly outline to the ethics board why we believe such a waiver is warranted.

1. The only change any patient will make in this trial is to a medication timing with evidence for greater safety (i.e. timing will not change for control institutions).
2. Patients and their families are not currently consulted about what time of day their medications are administered.
3. Current practice is to generally ignore the time of day patients took their blood pressure medication pre-admission and to administer those pills at an arbitrary time of the facilities choosing (typically morning for once daily medication).
4. Patients/families/primary care providers will be notified of the change in policy and given the opportunity to exempt their loved one / patient from participating.

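### Age enters the primary model and 13 other models only as under or over 70; a continuous term would use the same single degree of freedom and recover a little precision

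*Combined protocol and SAP*

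**What the plan says.** SAP Table 2 (under Selecting regression covariates) begins the primary model's covariates with "Age <70, Gender, Facility/Level of Care specific mortality rate (prior 3 years". The list ends "Charlson score, Facility, Total number of non-BP medications, Total number of BP medications, CHF, COPD, CKD, stroke, diabetes, CAD, sleep apnea", and age does not appear again.

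The protocol's Statistical Analysis paragraph uses the same coding, "using multiple patient level covariates including: Age <70, Gender, Location (Edmonton / Calgary / Other", so the two documents agree and the choice is prespecified. The row for unplanned hospitalisation or ED visit has it too: "Charlson score, Age < 70, Gender, Total number of non-BP medications, Total number of BP medications, CHF, COPD, CKD, Diabetes".

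The protocol's Baseline Data list names age with no categories, so exact age appears to be held. Neither document explains the cut at 70.

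On what covariates are expected to contribute, the protocol's Power/Sample Size section says "we have several covariates that are likely to be predictive of each outcome", and singles out level of care.

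**The concern.** The primary outcome includes all-cause death in frail residents, so age could plausibly predict it. A single cut at 70 treats a resident of 72 and one of 98 alike. If most residents are well above 70, the indicator carries little of the information in age.

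Two things are at stake. In a Cox model, leaving out prognostic variation pulls the estimated hazard ratio slightly towards 1 and costs some power, while the protocol hopes for extra power from its covariates. Also, randomisation is unstratified, so an age difference arising by chance among residents over 70 is not adjusted for.

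**Working it through.** **1. Which models use the coding.** Table 2 covers 18 outcomes. Age <70 is in 14:
- the primary outcome, and all-cause mortality by reference to it (2);
- unplanned hospitalisation/ED visit, fracture, incontinence and skin ulceration (4);
- deteriorated cognition (1);
- behavioural symptoms, and four medication, restraint and mood outcomes by reference to that row (5);
- two cost outcomes (2).

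The other four (stroke, MI/ACS and CHF hospitalisation, and falls) have no age term.

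**2. The plan's event target.** Inputs from the protocol: a 27.6% difference read as HR 0.724, 80% power, p of 0.05 (two-sided assumed), 1:1 allocation. Schoenfeld: 4 × (1.960 + 0.842)² / (ln 0.724)² = 4 × 7.849 / 0.1043 = 301. This matches the protocol. It is an unadjusted calculation, so the coding of age does not affect it.

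**3. Degrees of freedom.** The SAP allows one covariate per 10 outcomes: 301/10 gives 30. The primary list has 17 single-df terms, counting Age <70, plus Facility. Linear age also uses one df, so the rule gives no reason to dichotomise. A 3-knot restricted cubic spline uses two, one more than now.

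**4. Information kept by the cut.** No mean, SD or share under 70 is given. The nearest indication is that recruitment was projected from medication use in Canadians aged 80 and over. For age ~ Normal(mean, SD), with z = (70 − mean)/SD and p = Φ(z), the squared correlation between age and the indicator is φ(z)²/[p(1 − p)]. For mean 84, SD 8: z = −1.75, p = 0.040, and 0.0863²/(0.040 × 0.960) = 0.194. So about 49 of 1232 residents would be under 70, and 81% of the linear information would be lost.

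| Assumed mean, SD | Share under 70 | Kept | Lost |
|---|---|---|---|
| 78, 10 | 21.2% | 50.3% | 50% |
| 78, 12 | 25.2% | 54.1% | 46% |
| 80, 7 | 7.7% | 29.2% | 71% |
| 80, 12 | 20.2% | 49.2% | 51% |
| 84, 8 | 4.0% | 19.4% | 81% |
| 88, 7 | 0.5% | 4.2% | 96% |
| 88, 12 | 6.7% | 26.9% | 73% |

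**5. Effect on power.** Cox simulation: 1232 patients, stop at 301 events, HR 0.724, log-hazard linear in age, 1500 runs per scenario, the same data sets for each coding, no other covariates. The age effects (log-HR per year) are assumed.

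| Mean, SD | Log-HR per year | Age <70 | Continuous | Gain (points) |
|---|---|---|---|---|
| 80, 10 | 0.03 | 0.769 | 0.777 | 0.8 |
| 80, 10 | 0.05 | 0.765 | 0.783 | 1.8 |
| 80, 10 | 0.07 | 0.739 | 0.781 | 4.2 |
| 84, 8 | 0.03 | 0.793 | 0.796 | 0.3 |
| 84, 8 | 0.05 | 0.771 | 0.779 | 0.8 |
| 84, 8 | 0.07 | 0.778 | 0.794 | 1.6 |
| 86, 7 | 0.03 | 0.810 | 0.808 | −0.2 |
| 86, 7 | 0.05 | 0.782 | 0.800 | 1.8 |
| 86, 7 | 0.07 | 0.769 | 0.779 | 1.0 |

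Monte Carlo error is about 1 point per estimate. Attenuation is slight: in the strongest case (80, 10, 0.07) the average HR was 0.736 with the indicator and 0.722 with continuous age.

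**6. Chance imbalance.** With 616 per arm and SD 8 (assumed), the standard error of the difference in mean age is 8 × √(2/616) = 0.46 years. At 0.05 per year that moves the log-HR by about 0.02. The log-HR's own standard error at 301 events is 2/√301 = 0.115, so a typical imbalance is about one-fifth of a standard error.

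**The case against.** The strongest reply is that this is a prespecified choice, the same in both documents, with little effect. Most of that stands.

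- A reader might infer that very few residents are under 70. The documents do not say so. There is no age limit for entry, and supportive-living residents, whom the protocol expects to live longer, are included. At mean 78 with SD 10 to 12, a fifth to a quarter would be under 70.
- A reader might infer that most of the prognostic value of age is lost. The calculation in step 4 concerns the variance of age and uses no outcome data. It equals prognostic value only if age is near normal and log-hazard near linear in age. What matters in the model is what age adds to the Charlson score, prior hospital use, admission status, facility mortality rate and comorbidities. Terms correlated with age may recover part of the loss.
- A reader might infer that the design power depends on the coding of age. It does not. The 80% figure assumes no useful covariates, and the one covariate named as a source of extra power is level of care.
- Chance imbalance is a small matter, as step 6 shows, and the confidence interval already allows for it.

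What the reply leaves standing is that no reason is given for the cut, and that the alternative uses the same degree of freedom. The authors may have wanted to mark atypical younger residents, but the SAP does not say so.

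**Conclusion.** The point holds as a modest efficiency gain at no cost. That age appears only as Age <70 in 14 of 18 models, without a stated reason, is plain from the text. The 51% to 96% loss of linear age information rests on assumed normal ages with mean 80 to 88 and SD 7 to 12, and falls to 46% to 50% at mean 78 with SD 10 to 12. The simulated power cost of about 0 to 4 points, under 2 in eight of nine scenarios, rests further on assumed age effects and on a model without the other covariates.

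It would be wrong to read this as a flaw in validity. Allocation is randomised, so the coding does not bias the treatment comparison or inflate type I error, and the 301-event target is unaffected.

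**What to change.** In every Table 2 row that now lists Age <70, including those that inherit it by reference, replace it with age at randomisation as a continuous linear term in the same place in the order. Permit a 3-knot restricted cubic spline only where the event count leaves room for the extra degree of freedom without displacing a later covariate. This matters most for outcomes with few events, and wherever Facility takes up much of the allowance. Leave the four rows with no age term as they are, and keep the under-70 category for describing the sample.

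If unblinded analysis has already begun, as the October 2024 entry in the amendment log indicates, keep the prespecified model as primary and report the continuous-age model beside it as a labelled sensitivity analysis.

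The cost is a change of SAP wording and a rerun of the affected models. No new data are needed if exact age is held, as the Baseline Data list suggests. The linear term uses no extra degree of freedom.

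### The SAP's primary model has no resident-level term for level of care or dementia, both in the protocol's model, and its later covariates depend on an unstated number of facilities

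*Combined protocol and SAP*

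**What the plan says.** **Protocol.** Under Plan for Data Analysis, the covariates of the primary proportional hazards model include each resident's Level of Care Designation (five categories), and the list ends "Total number of BP medications, Dementia". The protocol has facilities supply the level of care of newly eligible residents and gives the reason: "The purpose of this data is to allow for adjustment of this variable". The Power/Sample Size section says that additional power will come partly from "covariates that are likely to be predictive of each outcome", and singles out level of care among them.

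**SAP, Selecting regression covariates.** The cap is: "Analyses of dichotomous outcomes will use a maximum of 1 covariate per 10 outcomes". The order is fixed: "We will always use the maximum number of covariates possible, selected in the order given". There is also a skip rule: "if one covariate has too many levels to be accommodated" by the outcomes that remain, it is passed over and selection continues.

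**SAP, Table 2, primary outcome.** The list starts with eight single-slot covariates. The third is a prior three-year mortality rate specific to facility and level of care. It then runs "Charlson score, Facility, Total number of non-BP medications", followed by number of BP medications, CHF, COPD, CKD, stroke, diabetes, CAD and sleep apnea. All-cause mortality uses the same list. Level of Care appears as its own covariate only in the cost models, where a footnote gives four levels. Dementia appears nowhere in Table 2.

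**The concern.** There are two separate points.

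1. The protocol commits to adjusting the primary outcome for each resident's level of care and for dementia, and it sets up data collection for the first. The SAP's primary model carries level of care only as a group-level rate and has no dementia term. It gives no reason for the change.

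2. Facility has many levels but stands ahead of nine single-slot resident-level covariates in a list that is filled in order up to a cap. The fitted model can therefore turn on how many facilities took part. Over part of the range each further facility removes one more clinical covariate. One facility beyond that range, the skip rule drops Facility and brings all nine back.

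Treatment is randomised, so neither point threatens bias in the treatment comparison. What is at stake is some precision and a primary model whose content is known in advance.

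**Working it through.** **Inputs**
- Target of 301 primary events (protocol, Outcomes and Power/Sample Size).
- One covariate per 10 events, filled in order with a skip rule (SAP, Selecting regression covariates).
- Table 2 order: 8 single-slot covariates, then Facility, then 9 single-slot covariates.
- Facility is taken to cost F - 1 slots for F facilities. The SAP does not say how a multi-level covariate is counted, so this is an assumption.
- F is not given. The protocol names six organisations, says most have several facilities, and expects more to join.

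**The 301 events.** Reading the 27.6% difference as a hazard ratio of 0.724, with two-sided 5%, 80% power and 1:1 allocation:

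4 × (1.960 + 0.842)² / (ln 0.724)² = 31.4 / 0.1043 = 301.

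The plan's figure is reproduced, with no covariate in the calculation.

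**Slots at 301 events.** The cap is 301/10, rounded down, which is 30. After the first eight, 30 - 8 = 22 remain. Facility fits if F - 1 ≤ 22, that is F ≤ 23. The nine later covariates all fit beside it if 22 - (F - 1) ≥ 9, that is F ≤ 14.

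| Facilities (F) | Facility in the model? | Later covariates lost |
|---|---|---|
| 14 or fewer | yes | 0 |
| 15 | yes | 1 (sleep apnea) |
| 18 | yes | 4 (also CAD, diabetes, stroke) |
| 21 | yes | 7 (also CKD, COPD, CHF) |
| 22 | yes | 8 (also number of BP medications) |
| 23 | yes | 9 (also number of non-BP medications) |
| 24 or more | no, skipped | 0 |

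If the treatment term also uses a slot (cap 29), the range with loss becomes 14 to 22.

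**Fewer events.** All-cause mortality uses the same list and cannot have more events than the composite. Its event count is not given. At an assumed 250 events (cap 25) the range with loss is 10 to 18 facilities; at an assumed 200 (cap 20) it is 5 to 13. The first eight covariates survive in all these cases.

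**Would the missing terms fit?** There are 8 + 9 = 17 single-slot covariates. Level of care adds 3 slots on the SAP's four levels, or 4 on the protocol's five. Dementia adds 1. The total is 17 + 3 + 1 = 21, or 17 + 4 + 1 = 22, of 30. So the cap does not explain their absence.

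**Moving Facility last instead.** With the added terms, 30 - 21 = 9 slots remain (or 30 - 22 = 8), so Facility fits only up to 10 (or 9) facilities. At 11 to 14 (or 10 to 14) this would drop Facility where the present list keeps everything.

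**Possible gain.** Cox fits were simulated at a hazard ratio of 0.724 with 301 events in 700 to 1200 residents. Gain was measured as (mean adjusted z / mean unadjusted z)² - 1. Adding predictors with a residual log-hazard SD of 0.3 gained about 1-5% information, which is 301 × 0.01 to 301 × 0.05, or about 3 to 15 events' worth. With an SD of 0.5 the gain was about 7-14%, or about 21 to 42 events' worth. Both SDs are assumptions. The simulations add predictors freely and do not model exchanging them for Facility.

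**The case against.** The strongest reply is that the SAP list is predefined, ordered and not stepwise, that a later SAP may revise a protocol's covariates, and that randomisation protects the comparison under either list. All of that stands, and it keeps the point small. A reader might still infer four stronger things that the documents do not support.

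- **That the SAP ignores level of care.** It does not. The facility and level-of-care mortality rate is third and is never displaced. What is missing is the resident's own designation as a term.
- **That the cap can remove the most useful adjustment.** This is not shown. Charlson score, prior hospital days, prior ED visits and the mortality rate all precede Facility and always stay. Sleep apnea, CAD and diabetes go first. Seven of the nine covariates at risk were not in the protocol's model at all. The two that correspond to it, the medication counts, are lost only at 22 and 23 facilities.
- **That planned power is given up.** The power section says its calculation assumes no useful covariates and treats any gain as extra and not calculable. The 80% is unaffected.
- **That Facility is redundant beside the mortality rate.** A three-year historical rate cannot capture current outbreaks or differences in how and when each pharmacist acted on the allocation list, and randomisation was not stratified. Adjusting for Facility is defensible; the difficulty is the way it competes for slots.

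Two limits also stand. Displacement at 301 events needs 15 to 23 facilities, which cannot be checked. And the documents do not list the components of the Charlson score, so they do not show how much of dementia it already carries.

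**Conclusion.** The point holds in two parts. The first is unconditional: the protocol's primary model has resident-level terms for level of care and dementia, the SAP's primary model has neither, no reason is given, and there is room for both at 301 events. The second is conditional: with 15 to 23 facilities, Facility displaces one to nine later covariates; with 14 or fewer, or 24 or more, it displaces none.

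The consequence is a modest loss of precision and a model that can change sharply with one more facility (none of the nine at 23, all nine at 24). It is not bias, and it is not a shortfall against the stated power. The slot counts rest on the 301-event target, which the SAP text does not restate, and on counting Facility as F - 1 slots. The size of the gain rests on assumed predictor strength. This is a desirable improvement, not a serious flaw.

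**What to change.** In the primary and all-cause mortality models:

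- Handle Facility as a Cox stratum, so that it uses no slot and the covariate set no longer depends on the number of facilities.
- Add Level of Care and Dementia directly after Charlson score. This uses 21 slots on the SAP's four levels or 22 on the protocol's five, which needs 210 or 220 events to fit in full. If all-cause mortality has fewer, the last-listed covariates drop first.
- State the number of facilities, how multi-level covariates and the treatment term count against the cap, and why the list differs from the protocol's.

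If the list is locked, keep Table 2 as the primary analysis and report this as a labelled sensitivity analysis. The amendment log's October 2024 entry shows that outcome results had been seen by then, so a change made after that date belongs there.

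The cost is small, because the variables are already collected. The downsides are four or five slots, and little information from facilities with very few events. There is also overlap with the facility and level-of-care mortality rate: within a facility stratum that rate varies only between levels of care, so beside level-of-care terms it adds less. Simply moving Facility to the end of the list is a weaker option, for the reason shown in the working.
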